### Training of USA’s APPs

Three outpatient APPs from the Department of Otolaryngology at Children’s Hospital Colorado with varying length of tenure and training in otoscopy (≥7 years of clinical experience) were trained in reading video-otoscopic images using didactic in-person training methods to identify the 14 possible otoscopic signs described in box 1.

### Patient and public involvement

No patient and public involvement took place in the design, or conduct, or reporting, or dissemination plans of the research.

### Statistical analysis methodology

Demographic attributes and potential risk factors derived from the Parent Questionnaire will be analysed to determine which ones should be included in the multivariate analyses. A p value <0.15 will be used to select the ‘significant’ variables. ORs will be computed for the dichotomous categorical variables, using a Cochran’s Mantel-Haenszel statistic to compute the p value. Continuous variables and categorical variables with more than two categories will be analysed using Student’s t-test or Wilcoxon rank-sum test. A rank-sum test will be used when the assumptions required for the t-test are not met. When there are significant differences in ear disease classification between the vaccine and placebo group, then a multivariate logistic regression model will be derived to identify the vaccine efficacy for the 11-valent pneumococcal conjugate (11PCV) vaccine, and significant effects for the covariables.

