### Subjects of the study

The study cohort consists of a potential of over 12 000 Filipino children who were enrolled in a pneumococcal vaccine trial conducted in Bohol 2000 to 2004 between the ages of 6 weeks and 10 weeks. For the current study, these same subjects will be approximately between 16 years and 20 years of age.

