#### Case report form (CRF)

Each research subject has an original paper CRF, which contains patient identifiers and clinical information entered by the research personnel following a parental interview with ear-specific medical history (ie, ear infection, discharge, TM perforation and hearing loss). CRFs collected during the week are uploaded by the research nurse into a Research Electronic Data Capture (REDCap) database hosted at the University of Colorado Denver School of Medicine, Aurora, Colorado, USA.

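### The vaccine efficacy model takes covariates from a parent questionnaire by p<0.15, with no bar on variables that vaccination can affect, so the reported efficacy could be pulled towards the null

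*Protocol article*

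**What the plan says.** The Statistical analysis methodology section of the Protocol article sets three rules.

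- Source of covariates: besides demographic characteristics, "potential risk factors derived from the Parent Questionnaire will be analysed to determine which ones should be included in the multivariate analyses".
- Selection: "A p value <0.15 will be used to select the ‘significant’ variables".
- Use: if the arms are found to differ significantly in ear disease class, "then a multivariate logistic regression model will be derived to identify the vaccine efficacy for the 11-valent pneumococcal conjugate (11PCV) vaccine".

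The section names no other efficacy estimate. It does not restrict the candidates to variables fixed before vaccination, and it does not say whether the p<0.15 screen is against the outcome or against the arm.

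On timing, Subjects of the study says the children were "enrolled in a pneumococcal vaccine trial conducted in Bohol 2000 to 2004 between the ages of 6 weeks and 10 weeks", and adds: "For the current study, these same subjects will be approximately between 16 years and 20 years of age".

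The Parent Questionnaire is named only in the statistical section, without a date or a list of items. The one parental data collection that the article describes is in the Case report form section. There the research personnel complete the form after a "parental interview with ear-specific medical history (ie, ear infection, discharge, TM perforation and hearing loss".

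That history is also used to build the outcome. The section on video-otoscopy and diagnosis classification combines it with otoscopy and tympanometry to reach the diagnosis. The section on incomplete data assigns chronic suppurative otitis media to an ear when the form records otorrhoea and nothing else is available.

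**The concern.** The study asks whether a vaccine given in infancy prevents the late consequences of otitis media. Ear infection and discharge between infancy and adolescence are the route by which it would do so. Perforation and hearing loss are the late consequences themselves, or close to them.

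A model holding the vaccine together with past ear disease does not estimate the total effect of randomisation. It estimates the part of the effect that does not pass through past ear disease, and that part can be small or nil when the vaccine works. A screen that keeps strong predictors of ear disease would favour exactly these variables. Where the same history helps define the diagnosis, one item could also stand on both sides of the regression.

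At stake is the headline efficacy figure and its confidence interval.

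**Working it through.** The article gives no event rate, effect size or power figure, so there is none to reproduce. The check has a textual part and an illustration.

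**Textual chain.** Stated outright: the questionnaire as source, the p<0.15 rule, the logistic model as the source of efficacy, randomisation at 6 to 10 weeks, and an interview about ear history in the current study at about 16 to 20 years. Inferred: that the Parent Questionnaire belongs to that data collection, and that its candidate risk factors include the ear history.

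**Assumed inputs.** Let M be a parent-reported history of ear infection or discharge.
- M in 20% of placebo subjects and 14% to 18% of vaccine subjects
- disease in 8% of subjects without M
- odds ratio of M on disease 3 to 10
- disease treated as yes/no, equal arms, no unmeasured common cause of M and disease
- efficacy read as 1 − odds ratio
- N = 12 000 (the potential cohort) or 8 000 (an assumed figure after attrition)

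**Worked example, full mediation** (M 20% vs 14%, odds ratio of M 10, N = 12 000).
1. Odds of disease without M: 0.08/0.92 = 0.0870. With M: 0.870, so risk 0.870/1.870 = 0.465.
2. Placebo risk: 0.80 × 0.08 + 0.20 × 0.465 = 0.157.
3. Vaccine risk: 0.86 × 0.08 + 0.14 × 0.465 = 0.134.
4. Unadjusted odds ratio: (0.1339/0.8661)/(0.1570/0.8430) = 0.83, an efficacy of 17%.
5. Preliminary test: pooled risk 0.1455, standard error √(2 × 0.1455 × 0.8545/6000) = 0.00644, z = 0.0231/0.00644 = 3.59. Power at two-sided 5% is Φ(3.59 − 1.96) ≈ 0.95, so the model would usually be fitted.
6. Screen: M is present in (0.0930 + 0.0651)/(0.1570 + 0.1339) = 54% of diseased subjects and 11% of the others. It passes p<0.15 against outcome with probability about 1.00, and against arm (20% vs 14%) also about 1.00.
7. Adjusted odds ratio: within each level of M the risk is the same in both arms (8% and 46.5%), so it is 1.00 and the efficacy is 0%.

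**Range over the assumed inputs.**

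| | Unadjusted OR | OR with M in the model | Power of the preliminary test |
|---|---|---|---|
| Full mediation | 0.83 to 0.97 | 1.00 | 0.06 to 0.95 |
| Direct OR of 0.90 remains | 0.76 to 0.88 | 0.90 | 0.41 to 1.00 |

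M passes the screen with probability about 1.00 against outcome and 0.80 to 1.00 against arm, so it matters little which is meant. With a direct effect, the share of the log odds ratio lost is 1 − ln(0.90)/ln(0.759) = 62% at one end and 1 − ln(0.90)/ln(0.878) = 19% at the other.

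**The case against.** Four points can be made for the plan.

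**The mediators are not shown to be candidates.** The questionnaire and the case report form have different names, no section equates them, and an article may leave the item list to the full protocol. The diagnosis sections treat ear history as an input to the outcome, not as a risk factor. This stands as a limit: a reader might infer that ear history will enter the model, but the documents support only that nothing prevents it. Leaving the list to another document does not cure the stated rule, which admits any questionnaire risk factor that passes the screen.

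**The model comes second.** It is fitted only after a significant difference between the arms, and that comparison is described without covariates. This also stands. A reader might conclude that the randomised test is lost; it is not. But the preliminary test does not protect the efficacy figure, which comes from the model.

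**Complete loss of the effect is an extreme case.** It needs full mediation, and with weak effects the model would often not be fitted. At 5.4% vs 4.8%, for example, z = 0.006/√(2 × 0.051 × 0.949/6000) = 1.49, about 32% power at N = 12 000. With partial mediation the result is attenuation.

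**Screening by p-value may be nearly harmless.** One might say that the p<0.15 rule by itself invalidates the p-value and interval. It does admit at least one of k irrelevant independent candidates with probability 1 − 0.85^k, which is 0.56, 0.80 and 0.96 for k = 5, 10 and 20. But irrelevant covariates unrelated to arm barely move the estimate at this sample size. A simulation of 20 such covariates screened on outcome (4 000 subjects, 2 000 runs, linear approximation) gave a type I error of 0.060, against 0.057 without adjustment. Material invalidity is not shown. The harm lies in which variables may be admitted.

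**Conclusion.** The point holds in a conditional form. The article takes vaccine efficacy from a model whose covariates are chosen by p-value from questionnaire risk factors, with no exclusion of variables that vaccination can affect. If the ear history is among the candidates, it would very likely be selected, and the reported efficacy and its interval would be biased towards no effect.

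Under the assumed rates the loss runs from about a fifth to about three fifths of the log odds ratio when a direct odds ratio of 0.90 remains, and it is total only under full mediation. In the clearest case a trial could find a real difference (15.7% vs 13.4%) and then report an efficacy of zero. These sizes rest on assumed prevalences and odds ratios, not on figures in the article. Fixed characteristics such as sex would do no harm as covariates.

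**What to change.** Amend the statistical section along these lines:

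- The vaccine efficacy estimate is the randomised comparison, either unadjusted or adjusted only for a short list of covariates fixed before any unblinded analysis.
- That list is limited to variables vaccination cannot affect, for example sex, age at examination, and enrolment variables if they are available from the original trial. The article does not say whether they are.
- The p<0.15 screen is not used for the efficacy model.
- Ear infection, discharge, perforation, hearing loss and other post-vaccination items are kept for a separate analysis, labelled as a risk-factor analysis.

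It would also help to state when the Parent Questionnaire is taken and which of its items are candidates.

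The cost is wording only; no new data need be collected. The minor downside is less freedom to adjust the efficacy estimate for later exposures.

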### Video-otoscopy data and diagnosis outcome classifications

Video-otoscopy analysis leading to disease classification takes into account all otoscopic abnormalities associated with acute OM, chronic non-suppurative OM and CSOM, as well as a non-OM diagnoses (eg, otitis externa) summarised in box 1. APPs document findings rather than immediately arrive at a diagnosis. Each video-otoscopic image is associated with a tympanogram type as to simulate pneumatic otoscopy, a proxy for the gold standard to diagnose middle-ear effusion.^14 15^ The gold standard for the presence of middle-ear fluid is detected only by myringotomy; however, this being impossible, the proxy methodology used here is based on the decisions made by the senior paediatric otolaryngologist with over 30 years of performing otologic procedures for complications from OM, including tympanoplasties and mastoidectomies. Given it would be impractical and impossible for the paediatric otolaryngologist to view thousands of video otoscopies, experienced otoscopists (APPs) have been trained and validated in identifying otoscopic abnormalities listed in box 1.

Box 1List of video-otoscopic finds depicting physical findings associated with otitis mediaRedness of tympanic membrane (TM).Opacification not due to scarring (dullness, thickened and webbing).Bubbles or air-fluid interfaces or fluid.Abnormal TM colour: white, yellow, amber or blue.Fullness or bulging of TM.Thinned out area of TM or healed perforation seen in 360°.Tympanosclerosis/scarring.Perforation small (<25% of TM).Perforation large (≥25% of TM).Retraction/retraction pocket/generally thinned out but not healed TM.Retraction/pocket bottom not seen.Otorrhoea not due to otitis externa (moisture).Granulation tissue or squamous debris.Otitis externa.

All video otoscopies that are deemed as poor quality by the APP are reviewed by the otolaryngologist of the study and would remained classified as poor quality or into one or more of the following TM findings.

Video-otoscopic findings for each ear will then merged with the four tympanometric output parameters and clinical medical history to arrive at discreet diagnoses (figure 1). Four broad diagnostic categories with definitions include normal, mild, moderate and severe ear disease. If two ears of a subject have disparate levels of middle-ear disease, the subject would be classified as having the more serious form of ear disease for the purpose of analysis.

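### The plan sends all categorical variables with more than two levels to a t-test or rank-sum test; for unordered ones the p<0.15 screen then depends on arbitrary code numbers and can miss a real risk factor

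*Protocol article*

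**What the plan says.** All of this stands in the Protocol article under Statistical analysis methodology, except the last item.

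- What is screened: "Demographic attributes and potential risk factors derived from the Parent Questionnaire will be analysed" and the purpose is "to determine which ones should be included in the multivariate analyses".
- Threshold: "A p value <0.15 will be used to select the ‘significant’ variables".
- Two-level variables: "ORs will be computed for the dichotomous categorical variables, using a Cochran’s Mantel-Haenszel statistic to compute the p value".
- Everything else: "Continuous variables and categorical variables with more than two categories will be analysed using" Student's t-test or the Wilcoxon rank-sum test.
- Choice between those two: "A rank-sum test will be used when the assumptions required for the t-test are not met".
- The outcome is an ordered class (Video-otoscopy data and diagnosis outcome classifications): "Four broad diagnostic categories with definitions include normal, mild, moderate and severe ear disease".

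The article names no chi-square, Fisher or general-association test, and no other section restricts the multi-category rule to ordered variables.

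**The concern.** The t-test compares means and the rank-sum test compares ranks, each between two groups. A variable such as area of residence or type of fuel (illustrations only; the article does not name them) has neither a mean nor a rank until someone assigns numbers to its levels. Another numbering of the same data gives another p value. The stated fallback does not help, because the rank-sum test needs an ordering just as the t-test needs a scale. Nor does it help to treat the multi-level variable as the grouping factor, since each test handles only two groups.

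At stake is which covariates pass the p<0.15 screen, and so which effects the multivariate model can report. For an unordered variable, entry would turn partly on the data-entry codes.

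**Working it through.** The plan gives no figure of its own to reproduce here. All counts and risks below are illustrative assumptions. From the plan come only the two tests and the 0.15 threshold, taken as two-sided because the article does not say.

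**Step 1. One table, three codings.** Assume 500 subjects in each of two groups, spread over three unordered levels as 200/150/150 and 170/190/140.

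Pearson chi-square: the expected counts in each group are 185, 170 and 145, so

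X² = 2 × (15²/185 + 20²/170 + 5²/145) = 2.43 + 4.71 + 0.34 = 7.48 on 2 df, p = 0.024.

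This does not change with the codes. The means that the t-test compares do change:

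| Codes for the three levels | Mean, group 1 | Mean, group 2 | t-test p | Rank-sum p | Kept at p<0.15? |
|---|---|---|---|---|---|
| 1, 2, 3 | (200+300+450)/500 = 1.90 | (170+380+420)/500 = 1.94 | 0.435 | 0.383 | no |
| 2, 1, 3 | (400+150+450)/500 = 2.00 | (340+190+420)/500 = 1.90 | 0.046 | 0.042 | yes |
| 1, 3, 2 | (200+450+300)/500 = 1.90 | (170+570+280)/500 = 2.04 | 0.0085 | 0.0089 | yes |

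The other three orderings are mirror images of these and give the same p values. The same data are dropped or kept by labelling alone.

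**Step 2. How often a real risk factor is missed.** Assume N = 8,000 (below the potential cohort of 12,000, because the Discussion expects attrition), three equal groups, and a yes/no disease outcome. Simulated share of trials with p<0.15, nearly identical for the t-test and the rank-sum test:

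| Disease risk by group | Highest-risk group coded in the middle (1,2,3) | Other codings | Chi-square |
|---|---|---|---|
| 4/8/4% | about 10% | about 100% | about 100% |
| 4/8/5% | about 56% | about 100% | about 100% |
| 4/8/6% | about 97% | 94% or more | about 100% |

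The first row can be checked by hand. With risks 4/8/4, the diseased are spread 25/50/25%, so under codes 1,2,3 their mean code is 0.25×1 + 0.50×2 + 0.25×3 = 2.00. The non-diseased also average 2.00 by symmetry. The difference is exactly zero although one group has twice the risk. With codes 1,3,2 the diseased average 0.25×1 + 0.50×3 + 0.25×2 = 2.25, while the non-diseased average (0.96×1 + 0.92×3 + 0.96×2)/2.84 = 1.99, and the effect is visible.

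**Step 3. Variables with no effect.** With 5% risk in all three groups, N = 8,000 and 1,000 runs per coding, the two planned tests selected 12.5%, 15.1% and 17.3% under three codings; chi-square selected 14.5%, 17.0% and 17.5%. All lie around the nominal 15%.

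**The case against.** **The unordered variables are assumed.** The article does not list the questionnaire items. Those that it does name under Case report form (ear infection, discharge, perforation, hearing loss) read as yes/no items, which the odds-ratio rule covers. If every multi-level item is ordered, the rank-sum test is acceptable, and a t-test on scores can be defended as a trend test. This stands as a limit. It does not remove the defect, because the rule as written covers any multi-category variable, and demographic attributes commonly include unordered ones.

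**The 4/8/4 case is built to fail.** It has no linear trend under codes 1,2,3. This is fair, and is why a range is shown: at 4/8/6 little power is lost.

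**Stronger readings that the documents do not support.**

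- A reader might infer that null variables get selected through their coding. Under any fixed coding the false-selection rate stays near 15%, as Step 3 shows.
- A reader might infer that the vaccine effect is biased. The arms were randomised, so leaving out a baseline risk factor does not by itself confound that comparison. The multivariate model is also to be built only if ear disease differs significantly between arms.
- A reader might apply the sentence to the four-level ear-disease class. The sentence follows the screening of demographic and questionnaire variables and does not clearly reach the outcome. For an ordered class a rank-sum test would in any case be acceptable.

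**An unseen analysis plan or article condensation.** Neither excuses the rule: the article states a specific method for a specific type of variable, so this is not a detail left for elsewhere.

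**Conclusion.** The rule is wrong as written for unordered variables with more than two levels. For these the p value, and so passage through the p<0.15 screen, depends on arbitrary numbering. The loss ranges from nearly complete (selection about 10% against about 100% for chi-square) to slight (97%), depending on the pattern of risk and where the highest-risk level falls in the coding. These figures rest on assumed risks, equal groups, N = 8,000 and a two-sided test. That the screen will meet unordered variables at all is likely but not shown.

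The effect is confined to covariate screening and the secondary risk-factor results. Two-level and continuous covariates are not affected.

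**What to change.** Replace the sentence on continuous and multi-category variables with three rules:

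1. Unordered variables with more than two levels: Pearson chi-square, or the CMH general-association test.
2. Ordered categories: Wilcoxon rank-sum, or the CMH row-mean-scores test.
3. Continuous variables: Student's t-test, or rank-sum where its assumptions fail.

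State for each multi-level questionnaire item whether it is treated as ordered or unordered, before the screen is run.

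The cost is a short change of text and different options in standard procedures; the article already names SAS as the export format. No new data are needed, and the 0.15 threshold and the rest of the section can stay as they are for this purpose.

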**Trial registration number:**

ISRCTN 62323832; Post-results.

Strengths and limitations of this studyThis large-scale study involves data collection in the Philippines and data transfers to the USA; thereby, a completely novel population-based audiometric and otoscopic assessment methodology needs to be developed.This methodology allows for the efficacy evaluation of a randomised controlled trial of pneumococcal vaccine conducted between 2000 and 2004 on the long-term complications of otitis media (OM) (chronic suppurative OM and its sequelae on the hearing).Despite in-depth training of local nurses to collect data and USA’s advanced practice providers to categorise video-otoscopic data, this methodology contains some degree of human factors and subjectivity that may lead to bias.This methodology lacks the ability to resolve inferior quality data or missing data due to logistic and geographic constraints resulting in decreased usable data for analysis.

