## Discussion

The methodology discussed in this manuscript will be sed to analyse a potential cohort of 12 000 children previously enrolled in a pneumococcal vaccine trial in Bohol, Philippines, and will now be assessed 12–18 years later for the vaccine’s effects on otoscopic and audiologic endpoints. It is unique in several aspects: size of the cohort, clinical endpoints and complexity of data analysis.

The sample sizes of previously published randomised controlled pneumococcal conjugate vaccine trials have been clearly summarised by a recently published Cochrane Review.^19^ Our cohort of over 12 000 children to be assessed likely would be lowered since attrition might occur due to inability to locate the families due to relocation or immigration after 15–18 years, as well as parental refusal to participate. Regardless, the biggest pneumococcal vaccine trials were published by Black *et al* in 2000^20–22^ and Tregnaghi *et al*^23^ involving 37 868 and 24 000 subjects, respectively. Black’s study was conducted in the USA, and acute OM was the only ear-related outcome.^21^ The Tregnaghi *et al*’s study was done in Central and South American countries, but only 7214 children from Panama were included in the OM portion of the study.^23^ Prymula *et al* published an acute OM trial using an 11-valent pneumococcal vaccine conjugated to *Hemophilus influenzae*-derived protein D trial in 4968 subjects.^24^ This trial was conducted in the Czech Republic and Slovakia, and tympanocentesis and pneumococcal subtyping were done. A recent open label trial of maternal immunisation with a 23-valent polysaccharide pneumococcal vaccine in 227 indigenous mothers in the Northern Territory, Australia, showed no impact on OM-related infant outcomes at 7 months of age.^25^

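### The vaccine efficacy model is fitted only after a significant between-arm difference, so a non-significant result has no planned estimate or interval

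*Protocol article*

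**What the plan says.** Under Statistical analysis methodology, the protocol article first screens demographic attributes and risk factors for the multivariate analysis ("A p value <0.15 will be used to select the" variables to carry forward) and names the statistic for two-level variables: "ORs will be computed for the dichotomous categorical variables, using a Cochran’s Mantel-Haenszel statistic to compute the p value". It then turns to the vaccine: "When there are significant differences in ear disease classification between the vaccine and placebo group, then a multivariate logistic regression model will be derived". The same sentence gives the model's purpose: "to identify the vaccine efficacy for the 11-valent pneumococcal conjugate (11PCV) vaccine, and significant effects for the covariables".

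The strengths and limitations box states what the study is for: "This methodology allows for the efficacy evaluation of a randomised controlled trial of pneumococcal vaccine conducted between 2000 and 2004".

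On size, the Discussion speaks of a "potential cohort of 12 000 children previously enrolled in a pneumococcal vaccine trial in Bohol, Philippines" and expects that this number "likely would be lowered since attrition might occur due to inability to locate the families", among other reasons. The article gives no retained sample size, placebo-arm disease rate, expected effect, power, or significance level for the between-arm comparison.

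**The concern.** A preliminary significance test decides whether the main quantity of the study is estimated. This has two consequences.

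1. If the test is not significant, no estimate or interval is planned. In that case the interval is the study's answer, because it shows which sizes of benefit the data exclude and which remain open. A bare non-significant result does not separate evidence of no worthwhile effect from too little information.
2. If the test is significant, only samples with a large enough observed difference reach the model. At limited power such samples overstate a positive effect on average, and the nominal interval no longer has its stated properties given that selection.

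The rule is stated in the article. It is not a detail left to an analysis plan, and a plan that followed this sentence would carry the rule forward.

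**Working it through.** **Is there an ungated vaccine estimate elsewhere?** The Mantel-Haenszel odds ratios follow directly from the sentences on demographic attributes and risk factors, and they serve covariate selection. The article does not say they compare vaccine with placebo. No other section plans a vaccine effect or an interval. The conditional model is therefore the only planned source of VE.

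**Inputs.** The article has no figure to reproduce. Assumed: 4,000 evaluable per arm (8,000 of a potential 12 000), 1:1 allocation, a two-sided 0.05 pooled z test as the gate, a binary disease outcome, placebo risk of 3% to 15%, and true VE of 0%, 10% or 20%, with VE = 1 − RR.

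**Method.** For each scenario, simulate two-arm binomial trials and estimate VE in every trial. Then compare the mean over all trials with the mean over trials that pass the gate. Coverage uses the usual 95% interval on the log RR.

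| Placebo risk | True VE | Gate passed | Mean VE, all trials | Mean VE, given a pass | 95% CI coverage, given a pass |
|---|---|---|---|---|---|
| 3% | 20% | 38% | 19% | 30% | 94% |
| 5% | 20% | 58% | 20% | 25% | 96% |
| 10% | 20% | 88% | 20% | 21% | 97% |
| 15% | 20% | 98% | 20% | 20% | 97% |
| 3% | 10% | 13% | 9% | 26% | 78% |
| 5% | 10% | 18% | 10% | 22% | 86% |
| 15% | 10% | 48% | 10% | 14% | 95% |
| 3% | 0% | 5% | −1% | −5% | about 1% |

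Coverage over all trials, without the gate, is about 95% in every row.

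In the last row, passing trials split about evenly between apparent benefit and apparent harm. The mean absolute VE is about 31%. Those favouring vaccine average about 26%.

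**Chance that no VE is produced** = 1 − probability of passing. For true VE 20% this is 62% at 3% risk, 42% at 5%, 12% at 10% and 2% at 15%.

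**Sensitivity to retained numbers** (VE = 1 − OR, 5% placebo rate, true VE 20%). With 12 000 in total, 72% pass and the mean VE given a pass is 23%. With 6,000 in total, 43% pass and the mean is 28%.

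**What an ungated null result would show.** Take 6,000 per arm, a 5% rate in both arms and an observed OR of 1:

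- SE(log OR) = √[2 / (6,000 × 0.05 × 0.95)] = √(2/285) = 0.0838
- 95% CI for the OR = exp(±1.96 × 0.0838) = 0.849 to 1.178
- 95% CI for VE = 1 − OR = −18% to +15%

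The same formula with 3,000 per arm gives −26% to +21%. With 6,000 per arm it gives −29% to +23% at a 2% rate and −11% to +10% at 15%. As written, the article plans to report none of these.

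**The case against.** **The gate does not damage the test.** This is correct. The type I error of the between-arm comparison is unchanged. The defect lies in estimation and reporting.

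**A reader might infer that any reported efficacy is biased upward.** The documents do not support that. The inflation needs a positive true effect and limited power. It nearly disappears at 10% to 15% placebo risk with a true VE of 20%. With no true effect, the signed mean among passing trials is slightly negative (about −5% at 3% risk), and the exaggeration runs both ways. The four-level classification includes mild disease, so a disease rate well above 3% to 5% is possible.

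**A reader might also infer that the interval never has its nominal coverage once the gate is passed.** This too goes too far. At true VE 20% with 4,000 per arm, conditional coverage is about 94% to 97%. It fails materially at low power or with no effect.

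**The article does not forbid a crude estimate.** True: only the multivariate model is gated, and some vaccine-placebo comparison must come first. The article is also condensed, so crude reporting may be described elsewhere. What can be said is that this text plans no null-case estimate, not that it prohibits one. That does not remove the problem, because the sentence on VE sets an explicit condition and nothing in the article offsets it.

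**Conclusion.** The point holds in a limited form. The article ties its only planned VE estimate to a significant between-arm difference, so a non-significant comparison leaves no planned estimate or interval in a study presented as an efficacy evaluation. That part follows from the text and needs no assumption about event rates.

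The distortion after a pass is conditional, and its size cannot be fixed from the document. Under the assumptions above, a true VE of 20% is reported on average as 30% at 3% risk, which is 1.5 times the truth, and as about 20% at 15% risk. Conditional coverage is about 78% at 3% risk and true VE 10%, near 0% with no effect, and close to nominal at true VE 20%. Claims of universal upward bias or universal loss of coverage should not be made.

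**What to change.** In Statistical analysis methodology, delete the opening condition of the sentence on the logistic model and state instead:

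> A model comparing vaccine with placebo will be fitted for the ear disease classification outcome used in the between-arm comparison, and vaccine efficacy with its two-sided 95% confidence interval will be reported whatever the result of that test.

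The wording is tied to the outcome of the between-arm comparison because the article names four disease categories but no single binary endpoint. The text must therefore point to whatever outcome that comparison uses.

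The cost is one sentence in the protocol or analysis plan and a model that is already planned for the significant case. No extra data are needed. The change should be made before the arms are compared, so that the reporting rule cannot depend on the result.
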